#### Aim 1: Quantifying associations between MOUD use and social and ecological factors

To quantify the associations between MOUD use (e.g., methadone, buprenorphine, XR naltrexone) and individual, community, and treatment program organizational characteristics, we will use generalized linear mixed effects models (GLMM). The primary outcome of interest is whether an individual received MOUD during the treatment episode. We will include random effects to account for repeated measurements within individuals and clustering by program and county, and time fixed effects to address secular trends, such as the pre- and post-COVID-19 periods. We will test whether models can be simplified by replacing time fixed effects with time-related splines or power terms. We also will explore interactions among variables of substantive interest (e.g., varying the effect of criminal justice involvement on OUD treatment by community influences and program organizational factors). We will adopt a generalized estimating equations approach with robust standard errors to ensure the robustness of our findings. To address potential bias associated with correlations between predictors and random effects, we will utilize the Mundalk approach of mean-centering variables within county. A penalization approach (lasso regression) will be used for feature selection to address overfitting and collinearity. The validity of the approach will be ensured using cross-validation and sample splitting. Given the large sample size (>65,000) across multiple years, we are powered to detect conservative odds ratios (≥1.1) with 80% power at a two-sided alpha of 0.05 (assuming 10% overall prevalence of MOUD use). Higher prevalence will lead to improved power.

*Aim 1a*: *Associations with psychological and social determinants of health*. First, we will explore the association between MOUD use and psychological and social determinants of health at both the individual (e.g., housing status, comorbid mental health diagnoses) and community levels (e.g., social vulnerability index, program availability). For each group of measures, we will build distinct GLMMs. These models will be adjusted for age, sex, race, as well as other individual baseline and time-varying covariates (as specified in the measures table).

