#### Aim 2: Evaluating program organizational factors influencing OUD treatment retention

This objective focuses on analyzing program organizational characteristics associated with improved medication adherence and retention in OUD treatment among TA adults, while controlling for individual and community characteristics related to retention in care. Employing time-to-event analysis, a set of statistical methodologies focusing on the time until an event occurs, we will focus on a) discontinuation of MOUD use following initiation during the treatment episode and b) treatment completion as our event outcome of interest. To accommodate the longitudinal structure of these data, we will employ extended Cox models. We will assess the validity of the proportional hazards (PH) assumption for time-invariant variables through log-log plots, observed versus expected plots, goodness-of-fit testing, and the use of time-dependent variables. Variables not adhering to the PH assumption will be assessed for interaction with time and, if necessary, incorporated into the final Cox model. We will assume non-informative censoring, meaning that censoring and the event risk are independent after conditioning on observable features.

These models will yield hazard ratios, critical in evaluating the hypotheses stated. To mitigate confounding, we will introduce individual, program, and community-level variables into the model, yielding adjusted hazard ratios alongside point estimates and 95% confidence intervals. The extensive confounding measures at individual, program, and community levels collectively address bias stemming from omitted or uncontrolled confounding variables. We will conduct robust sensitivity analyses and explore variation in association strength due to plausible instruments for program selection, such as patient travel distance to programs and concurrent MOUD use among other individuals in the same community. To prevent overfitting, we will apply techniques outlined in Aim 1. As a sensitivity analysis to consider the multilevel structure of the data, we will deploy extended mixed-effects Cox models. An extended Cox model can incorporate time-dependent factors [99]. A mixed-effects Cox model can incorporate multiple fixed and random effects [100]. Specifically, we will include a fixed effect for each individual, program, and community-level variable defined above and random effects for repeated measures of an individual over time, program, and community.

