#### Aim 3: Examining program characteristics and adverse OUD-related events

Our final objective is to examine the association between treatment program organizational characteristics and adverse OUD-related events (AE) such as an SUD-related emergency department visit, including for overdose, while accounting for individual and community characteristics. Like Aim 2, we will employ time-to-event methods, focusing on the occurrence of the first adverse event. The adjusted hazard ratio of program structural factors, staff characteristics, and clinical care delivery features will be evaluated against a null hypothesis of 1. We will conduct sensitivity analyses akin to those described in Aim 2, ensuring the robustness of our results and conclusions. Applying the Lachin-Foulkes method to a study spanning 14 years, with variable drop-out rates, we determined that our sample size (>65,000) provides substantial power to detect clinically significant associations. Even under variable rates of attrition (10%-70%), we maintain adequate power to detect hazard ratios of 1.15 (or 0.87) with 80% power and a 5% type I error rate. Given the estimated study sample (>65,000), we are powered adequately to detect clinically meaningful associations.

*Aim 3a*: *Program structural factors and AE*. First, we will investigate the relationship between program structural elements (e.g., program size and type) and the occurrence of adverse OUD-related events (AE).

*Aim 3b*: *Program staff characteristics and AE*. Second, we will explore the connection between program staff attributes (e.g., professional degrees) and the incidence of adverse OUD-related events.

*Aim 3c*: *Clinical care process measures and AE*. Third, we will assess how clinical care processes (e.g., use of telehealth, counseling modalities) are associated with the prevalence of adverse OUD-related events.

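### Aims 2 and 3 leave program clustering to a sensitivity analysis, although the factors they test are program characteristics

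*Protocol article*

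**What the plan says.** All places are in the Analysis part of the protocol article.

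- **Aim 2, main model.** The model is chosen for the time dimension: "To accommodate the longitudinal structure of these data, we will employ extended Cox models". Individual, program and community variables enter as covariates, and the adjusted hazard ratios with 95% confidence intervals come from this model.
- **Aim 2, clustering.** "As a sensitivity analysis to consider the multilevel structure of the data, we will deploy extended mixed-effects Cox models". That model has "random effects for repeated measures of an individual over time, program, and community".
- **Aim 2, link to Aim 1.** The techniques carried over concern overfitting: "To prevent overfitting, we will apply techniques outlined in Aim 1".
- **Aim 3.** "Like Aim 2, we will employ time-to-event methods, focusing on the occurrence of the first adverse event". Its sensitivity analyses are modelled on those of Aim 2. On the hypotheses: "The adjusted hazard ratio of program structural factors, staff characteristics, and clinical care delivery features will be evaluated against a null hypothesis of 1".
- **Aim 1, for contrast.** In the main model: "We will include random effects to account for repeated measurements within individuals and clustering by program and county". As a further check: "We will adopt a generalized estimating equations approach with robust standard errors to ensure the robustness of our findings".

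**The concern.** Aims 2a–c and 3a–c ask whether program structure, staffing and clinical process are related to retention and adverse events. Patients of one program largely share these values. They also share whatever else makes that program better or worse, and the measured covariates will not capture all of it. For such an exposure the information is limited by the number of programs as well as by the roughly 65,000 patients. A Cox variance that ignores program counts patients only.

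The article gives each model a job: the extended Cox model handles time, and the mixed-effects Cox model handles levels. Only the first is the main analysis. Aim 1b studies the same kind of exposure with program and county random effects in its main model, and no reason is given for treating Aims 2 and 3 differently.

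At stake is whether chance differences between programs are reported as quality factors in results meant for policy makers. If the two models disagree, the plan gives priority to the one that does not address clustering.

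**Working it through.** **1. The plan's own figure.** Aim 3 states a detectable HR of 1.15 (or 0.87) at 80% power and 5% type I error. With Schoenfeld's formula, two-sided 5% (the article gives the sidedness only for Aim 1) and a 50:50 exposure split:

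events = 4 × (1.960 + 0.842)² / (ln 1.15)² = 1,608; for HR 0.87, 1,619.

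1,608 events are 2.5% of 65,000 patients, or 8.2% of the 19,500 left if 70% attrition is read as complete loss. With 10% exposed, 4,465 events (6.9% of 65,000) are needed. So HR 1.15 is plausible for independent patients. It cannot be reproduced exactly, because the event rate, accrual pattern and exposure share are not given. No term for clustering is named.

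**2. Effect of ignoring program.** For a program-level exposure and a program random effect on the log-hazard with standard deviation SD:

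- design effect DE ≈ 1 + SD² × (events per program)
- the unclustered standard error is too small by a factor √DE
- actual type I error of the nominal 5% test = 2 × [1 − Φ(1.96/√DE)]

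From the article: N = 65,000. Assumed, because not given: 400 programs (162.5 patients each), the event share, the SD, and an exposure constant within program.

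One cell in full (50% share, SD 0.2): events per program = 81.25; DE = 1 + 0.04 × 81.25 = 4.25; √DE = 2.06; 1.96/2.06 = 0.95; type I error = 34%.

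| Event share | Events per program | SD 0.1 | SD 0.2 | SD 0.3 |
|---|---|---|---|---|
| 50% | 81.25 | 14.5% | 34% | 50% |
| 20% | 32.5 | 9% | 20% | 32% |
| 10% | 16.25 | 7% | 13% | 21% |
| 2.5% (1,608 events) | 4.0 | 5.5% | 7% | 9% |

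With 1,000 programs (65 patients each) and a 50% share, there are again 32.5 events per program, so the 20% row applies. At 1,000 programs, a 10% share and SD 0.1, the error is 5.8%. For scale, SD 0.2 means a 90th-to-10th percentile program hazard ratio of exp(2 × 1.2816 × 0.2) = 1.67.

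**3. Check by simulation.** Cox model, null effect, half of 400 programs exposed, log-normal program frailty, about 65,000 patients and 11,300 to 12,000 events (about 18%), 200 runs per setting. At SD 0.1/0.2/0.3 the unclustered test rejected in 7/19.5/35.5% of runs; the formula at those event counts gives 8/18/31%. The program-clustered sandwich variance gave 4/7/4.5%.

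**4. Effect on the Aim 3 power statement.** Take a design with exactly the 1,608 events needed for HR 1.15 and 400 programs. With a valid clustered test the detectable HR is 1.15^√DE. DE = 1.04/1.16/1.36 at SD 0.1/0.2/0.3, which gives 1.153/1.163/1.177. With more events the starting value is below 1.15, so this formula must not be applied to the upper rows of the table. At a 20% share (13,000 events), 50:50 exposure and SD 0.3, the detectable HR is exp(2 × 2.802 × √(3.925/13,000)) = 1.10.

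**The case against.** **Independence is not stated.** A reader might infer that the plan treats patients of one program as independent. The article never says so; it names no variance estimator for the main Cox models, and a clustered sandwich variance would be compatible with its wording. A journal article may leave that detail to a full analysis plan. This stands, and it limits how firmly the point can be put. It does not remove the point, because the article does more than stay silent: it assigns the multilevel structure to a sensitivity analysis, in contrast to Aim 1.

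**The size could be small.** The event share matters as much as the number of programs. A 50% share may suit discontinuation of medication in Aim 2, but nothing in the article supports it for first adverse events in Aim 3. The calculation also has no covariates, whereas the plan adjusts for variables at all three levels, which would reduce the residual program variation. Both stand; hence the range.

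**Exposures are not all fixed within a program.** Program characteristics are assessed at each patient's admission, entry runs from 2012 to 2025, and Table 1 defines size by annual volume and telehealth by average monthly claims. Patients of one program can therefore have different values, and the inflation is then smaller. The table above fits program type or hospital affiliation better than telehealth volume.

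**The right model is already planned.** Readers would see a divergence if both models are reported. True, but the plan does not say which result then prevails, other than by calling one of them a sensitivity analysis.

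**Conclusion.** The point holds as a hierarchy that is the wrong way round. The main Cox analyses of Aims 2 and 3 name no allowance for program, and the model that has one is secondary. Followed as written, tests of program characteristics are anti-conservative whenever variation between programs remains after adjustment. The direction is sure under that condition; the size is not. Under the assumptions shown for 400 programs, the nominal 5% test runs from about 5.5% (few events, SD 0.1) to about 50% (half of patients with an event, SD 0.3).

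Two further readings go beyond the documents. One is that the study lacks power for HR 1.15: the event rate and number of programs are not given, and with enough events a clustered analysis could still reach that value. What can be said is that the stated figure names no design effect. The other is that a person-level random effect would be unidentifiable in the first-event model of Aim 3: the article lists that term only for the repeated measures of Aim 2, and for Aim 3 speaks only of similar sensitivity analyses.

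**What to change.** Before Aims 2 and 3 are analysed, name one of these as the main analysis for both:

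1. the extended Cox model with a sandwich variance clustered on program, which keeps the marginal hazard ratio; or
2. the mixed-effects Cox model with program and community random effects, already planned for Aim 2.

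Make the unclustered Cox model the sensitivity analysis. Restate the Aim 3 detectable hazard ratio of 1.15 (or 0.87) with an assumed number of programs, event share and between-program variation.

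No new data are needed, but the cost is more than wording. Confidence intervals become wider, the detectable hazard ratio becomes less favourable than the same calculation gives for independent patients, and under option 2 the hazard ratio is conditional on program and must be interpreted so.

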#### Aim 3: Examining program characteristics and adverse OUD-related events

Our final objective is to examine the association between treatment program organizational characteristics and adverse OUD-related events (AE) such as an SUD-related emergency department visit, including for overdose, while accounting for individual and community characteristics. Like Aim 2, we will employ time-to-event methods, focusing on the occurrence of the first adverse event. The adjusted hazard ratio of program structural factors, staff characteristics, and clinical care delivery features will be evaluated against a null hypothesis of 1. We will conduct sensitivity analyses akin to those described in Aim 2, ensuring the robustness of our results and conclusions. Applying the Lachin-Foulkes method to a study spanning 14 years, with variable drop-out rates, we determined that our sample size (>65,000) provides substantial power to detect clinically significant associations. Even under variable rates of attrition (10%-70%), we maintain adequate power to detect hazard ratios of 1.15 (or 0.87) with 80% power and a 5% type I error rate. Given the estimated study sample (>65,000), we are powered adequately to detect clinically meaningful associations.

*Aim 3a*: *Program structural factors and AE*. First, we will investigate the relationship between program structural elements (e.g., program size and type) and the occurrence of adverse OUD-related events (AE).

*Aim 3b*: *Program staff characteristics and AE*. Second, we will explore the connection between program staff attributes (e.g., professional degrees) and the incidence of adverse OUD-related events.

*Aim 3c*: *Clinical care process measures and AE*. Third, we will assess how clinical care processes (e.g., use of telehealth, counseling modalities) are associated with the prevalence of adverse OUD-related events.

## Discussion

Our study explores treatment quality outcomes for TA adults with OUD along three dimensions, encompassing the use of MOUD, treatment adherence and retention, and adverse event outcomes, such as overdose. We also will focus on the influence of organizational change and innovation on these outcomes, such as increased telehealth visits and flexibility in methadone take-home doses following onset of the COVID-19 federal public health emergency. By integrating large administrative datasets with insights from rigorous statistical analyses, our study will examine the socio-ecological factors influencing treatment quality and aid policy makers in establishing evidence-based standards for an understudied and vulnerable population.

With the number of TA adults seeking treatment for OUD on the rise, especially among those covered by Medicaid, this study has the potential to make an impact by improving the health outcomes of TA adults amidst the opioid crisis. One of our study’s strengths is that it is designed to study the quality of treatment for OUD that is specific to young adults. Adopting a socio-ecological perspective, we draw insights into how individual, program, and community-level characteristics impact how a specific population that is especially vulnerable to socio-ecological forces does over time. Given that OUD disproportionately affects individuals insured by Medicaid, the data linkage between the CDS and Medicaid claims is another key strength of the study.

We must acknowledge that our study has its limitations. The most critical limitation is that we will not be experimentally controlling for all factors related to program selection. Consequently, we will be tempered in making causal inferences about the associations we find [101, 102]. We address this limitation through the use of the rigorous statistical methods and sensitivity analyses described above. Studies of this type, which examine the impact of organizational quality in real-world settings, have a long tradition in informing both scientific practice and policy [102]. Another limitation of our study is that we do not compare the impact of multi-level factors on MOUD outcomes between TA and older adults, limiting our ability to discern if there are organizational factors that are more or less potently associated with MOUD outcomes for TA adults than for non-TA adults. Still, our study findings will yield important recommendations to engage and retain an underserved population in treatment at a pivotal life phase. Lastly, the administrative databases we use will not identify all aspects of care provision for OUD (e.g., staff decision-making and patient clinical experiences). Nevertheless, our study will be a valuable addition to the growing body of qualitative, ethnographic, and spatially oriented research that explores the impact of various mechanisms like social networks, institutional qualities, and structural vulnerability on substance-related risks and harms and treatment practices [103–105].

Over the past decade, there has been a significant increase in the prevalence of OUD among TA adults. Unfortunately, the existing OUD treatment framework inadequately serves this demographic, with lower rates of evidence-based treatment and increased early treatment attrition. Moreover, the heightened risk of substance-related adversities magnifies the issue. We need research to understand better the impact of existing types of care as well as inform policy makers, treatment providers, and the public about what individual, program, and community characteristics are associated with better quality of care. With the array of care options and the diversity inherent among TA adults, our study’s analytical methods will provide crucial information to address treatment gaps and disparities, benefiting this highly vulnerable age group.

## Status and timeline of the study

Access to both state treatment registry (CDS) and Medicaid claims has been acquired as of September 2023, but no data analysis has been done yet. Analysis is expected to start during the winter of 2023, after merging data from the two sources. Aim 1 analysis will begin during the winter of 2023, followed by Aims 2–3 concurrently. The study is set to be finished by the fall of 2025.
